## Abstract

**Background:**

Evidence to support use of cardiac resynchronization therapy (CRT) among patients with both heart failure (HF) and atrial fibrillation (AF) is largely limited to retrospective or post hoc subanalyses. Data from a prospectively enrolled and contemporary cohort are needed.

**Objective:**

We aim to better characterize the changes from baseline in HF patients with concomitant AF subsequently implanted with a 2-lead CRT-DX system capable of sensing in the atrium, aggregating diagnostics, and delivering CRT therapy. The primary objective of this study is to evaluate the percentage of all HF subjects with an improvement in a clinical composite score from pre-CRT implant to 12 months.

**Methods:**

The study is a US-based, prospective, observational multicenter clinical trial conducted at up to 50 sites and enrolling approximately 400 subjects with a follow-up period of 1 year. Multiple subject assessments, atrial rhythm status, and device interrogation will be collected at follow-up visits occurring at 3, 6, and 12 months postimplant.

**Results:**

A Clinical Events Committee will adjudicate subject HF events, arrhythmia events, death events, and all device-classified ventricular tachycardia and ventricular fibrillation episodes with treatment that are collected throughout the follow-up period. Their decisions are based on independent physician review of the data from sites and device interrogation.

**Conclusion:**

The BIO-AffectDX study aims to provide further insight into the expected outcomes from CRT treatment in patients with HF and AF.

Key Findings
▪The findings from the BIO-AffectDX study will help address knowledge gaps of cardiac resynchronization therapy (CRT) utilization in concurrent heart failure and atrial fibrillation (AF). With a specific focus on differences between AF subtypes, this prospective study evaluates the effectiveness of CRT in patients that have a standard CRT-D indication per current guidelines.▪The BIO-AffectDX study utilizes a clinical composite score to evaluate CRT effectiveness after 1 year of follow-up as compared to baseline prior to device implant. The study also aims to collect information to further understand the association between ablation for atrial fibrillation and CRT.▪The study utilizes a novel 2-lead CRT system that provides atrial sensing diagnostics, which allows for monitoring of atrial status. Atrial status will be correlated with procedures that may impact atrial rhythm, as well as spontaneous conversion events to further elucidate how these events impact CRT effectiveness.▪The results of the BIO-AffectDX study are expected to inform future societal consensus and guidance documents regarding the value of CRT in patients with both heart failure and atrial fibrillation.

## Introduction

### Prior studies of cardiac resynchronization therapy in atrial fibrillation patients

Heart failure (HF) and atrial fibrillation (AF) often coexist, with one condition occasionally predisposing the other. It is estimated that approximately 20% of patients with HF, and 25% of patients receiving cardiac resynchronization therapy (CRT), have some form of AF.^1^^,^^2^ CRT is a proven treatment shown to improve quality of life, functional status, and mortality in an indicated HF population.^3^, ^4^, ^5^ However, many early clinical trials evaluating the effectiveness of CRT excluded patients with AF, making it difficult to ascertain a benefit in this specific comorbid population. As a result, current guideline-concordant indications call for CRT in patients with AF as a class IIa level of evidence B, while patients with sinus rhythm are a class I level of evidence A indication.^6^

CRT effectiveness in patients with HF and AF has been evaluated in a limited number of studies with conflicting results.^2^^,^^3^^,^^7^, ^8^, ^9^ Interpretation of the existing data has relied heavily on secondary analyses of subgroups from randomized controlled trials and retrospective analyses of national registries. Furthermore, there is some limited evidence suggesting that CRT-D may reduce the frequency and duration of AF in patients with HF.^10^^,^^11^ More prospective data are needed to corroborate these findings.

Additionally, in a 2020 review of CRT research a panel of experts examined the existing clinical data related to CRT effectiveness in patients with HF with reduced ejection fraction and identified several evidence gaps related to CRT.^12^ Two of the top-tier gaps related to the effectiveness of CRT among patients with paroxysmal, persistent, and permanent AF and the association and role of atrioventricular (AV) node ablation on CRT effectiveness.

### Role of atrial lead in CRT

Since 2006, studies have consistently supported the concept that higher percentages of biventricular pacing are associated with improved patient outcomes, with optimal percentages ranging from 90% up to 100%.^13^, ^14^, ^15^, ^16^ Effective CRT pacing is difficult to achieve in the setting of AF, as loss of AV synchrony, uncontrolled ventricular rates, and a high percentage of fusion and pseudo-fusion beats can contribute to suboptimal delivery of CRT pacing.^17^ Traditional CRT-D systems have utilized 3 leads historically (atrial, right ventricular, and left ventricular [LV]). When a patient is indicated for atrial pacing support it is self-evident that an atrial lead is warranted and appropriate. This lead may also provide the added benefit of improving supraventricular and ventricular arrhythmias along with identifying atrial high-rate episodes. Additionally, implanters may prefer atrial placement at the time of CRT-D implantation to avoid a reoperation in the event a patient develops the need for pacing support at a later time. The decision to implant an atrial lead in patients without a need of atrial support does not currently reflect practices in the United States. Wide regional variation exists in the United States regarding when to place an atrial lead and there is evidence with implantable cardioverter-defibrillators (ICDs), at least, that nearly two-thirds of patients without a pacing indication are implanted with an atrial lead.^18^ The added procedural and long-term risks associated with this third lead are not insignificant, as studies have identified increased rates of periprocedural complications, in-hospital mortality, and complications within 90 days of device implantation.^19^ Additionally, it has been observed that implantation of atrial leads can be detrimental in that they can actually promote AF.^20^ These added risks combined present a challenge for current physicians considering the risk-benefit ratio of an atrial lead. Furthermore, the utilization of atrial pacing specifically in CRT patients without a clear need for atrial pacing is not well established.^21^ Additionally, the 2012 EHRA/HRS expert consensus statement on cardiac resynchronization therapy recommended using VDD/DDD mode with a base rate of 35–40 beats per minute to ensure permanent or nearly permanent atrial sensing and avoid atrial support altogether.^22^

### Two-lead CRT system

BIOTRONIK’s CRT-DX system can deliver CRT utilizing a novel 2-lead system that incorporates atrial sensing on the ICD lead for supraventricular tachycardia discrimination and AV synchronization, thus allowing for CRT delivery with fewer leads. The 2-lead CRT-DX systems are considered for patients without a need for atrial pacing, including those with permanent AF, and may preserve the benefits of sensing atrial activity without the need to implant an atrial lead.

Although experience with this system is limited, the emerging data are encouraging and support the safety of this system in carefully selected patients. Biffi and colleagues^23^ compared clinical and technical outcomes of 25 CRT-D recipients with 3-lead systems and 12 patients implanted with a CRT-DX. An absolute indication for atrial stimulation was observed in 1.2% of CRT recipients during a 3-year follow-up period. CRT response and chronotropic incompetence was evaluated and there was no difference between the 2 groups observed with respect to NYHA class improvement, peak cardiopulmonary performance, reverse remodeling, and the presence of chronotropic incompetence at 1 year. There were also no patients observed to develop a need for atrial pacing support at 3 years with an absence of atrial undersensing. Additionally, a recent subanalysis of 240 patients demonstrated significantly fewer complications and lower rates of inappropriate shock among patients implanted with a CRT-DX system while supporting similar health status outcomes as compared to patients implanted with a conventional 3-lead CRT system.^24^ However, it is difficult to extrapolate these findings to patients with AF, since AF history and ablation status within each cohort were unknown.

There is also some evidence that suggests patients in AF receiving CRT may experience a reduction in overall atrial burden and up to 10% of patients may spontaneously convert back to sinus rhythm.^25^ The CRT-DX system may offer an added benefit of providing appropriate detection of AF and mode switch capability and provide ventricular pacing support during pauses without the need and increased risk that is associated with an atrial lead. Compared to systems without a dedicated atrial lead, DX has been proven superior with regard to detection of atrial tachycardia / AF, which allows for earlier intervention.^23^^,^^26^ Based on the need for additional prospective data, the BIO-AffectDX Study is designed to evaluate the percent of subjects with 12-month improvement from pre-CRT implant in a large cohort of HF patients with AF implanted with a novel, 2-lead CRT system. The analysis particularly emphasizes a comparison of patient outcomes between the AF subtypes.

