## Objectives

The primary objective of this study is to evaluate the percentage of all HF subjects with an improvement in a clinical composite score (CCS) from pre-CRT implant to 12 months. Subjects will be stratified by paroxysmal, persistent, and long-standing persistent AF subtypes implanted with a 2-lead CRT-DX system.

Secondary objectives include the following: (1) to evaluate the rate of composite all-cause death and HF hospitalizations through 12 months; (2) to compare AF subtypes for CCS status, changes in Atrial Fibrillation Effect on Quality-of-Life Questionnaire, changes in Minnesota Living with Heart Failure Questionnaire, changes in NYHA, changes in 6-minute walk test, and changes in AF burden at 6 and 12 months; (3) to evaluate the proportion of subjects showing improvement from pre-CRT using a CCS at 6 months; (4) to evaluate the observed major complication rates from device implantation in this population at 12 months; (5) to evaluate the percentage of subjects converting to sinus rhythm at any time during the 12-month follow-up period, along with reason for conversion, both overall and by AF subtype.

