## Design

### General considerations

The BIO-AffectDX Study is a multicenter, prospective, observational, single-arm study designed to evaluate the rate of subjects showing improvement from pre-CRT using a CCS at 12 months in up to 400 HF subjects with paroxysmal, persistent, or long-standing persistent AF subtypes and a 2-lead CRT-DX system. This study is an industry-initiated clinical trial designed by a steering committee consisting of physicians (who also serve as investigators) in collaboration with the sponsor. Study subjects will be enrolled at up to 50 participating US sites. Target enrollment percentages are 50%, 30%, and 20% of the total study population for paroxysmal, persistent, and long-standing persistent AF, respectively. Patients will be screened for the inclusion and exclusion criteria and sign an informed consent prior to baseline assessments, which include quality-of-life assessment, 6-minute walk test, NYHA class assessment, rhythm collection, and pertinent medical history. Subjects will be implanted with a CRT-DX (BIOTRONIK SE & Co KG, Berlin, Germany) pulse generator and DX ICD (BIOTRONIK SE & Co KG) lead, plus an LV lead within 30 days following informed consent. All subjects eligible for the study will receive a new (de novo) implant or undergo an upgrade from an existing single-chamber ICD system that includes a DX ICD lead. Subjects will be seen for follow-up visits at 3, 6, and 12 months postimplant. In addition, details on ablation or cardioversion procedures occurring during follow-up will be collected, which include recording atrial rhythm pre- and postprocedure, the cardioversion and catheter ablation procedure date, type and success as determined by the investigator, and device programming and settings, as well as device diagnostics, electrical parameters, and programmed parameters. HF, all-cause mortality, and arrhythmia events will be collected and adjudicated by independent event committees. All-cause death and HF hospitalization among all subjects will be calculated as raw number and percentage of subjects at 12 months. Mortality will be assessed by each site by a thorough review utilizing all available medical records. HF events will include HF hospitalization and worsening HF events without hospitalization. Adjudicated arrhythmic events will be limited to device-classified ventricular tachycardia (VT) and ventricular fibrillation (VF) episodes with shock treatment. Device-classified VT and VF episodes with antitachycardia pacing but no shock that transmitted and are available on home monitoring will also be adjudicated. Study results will be hypothesis generating, given the observational design of the study without use of a prospective control arm.

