
### Sample size justification

There is no formal inferential analysis scheduled for the primary objective. The study was designed to limit the number of subjects involved, while still providing CRT-DX therapy to a sufficiently large subject population to ensure a representative and statistically meaningful sample. It is anticipated that at least 400 subjects will be implanted and followed through 12 months postimplantation at up to 50 US sites. The sample size required to assess the primary objective is based on the precision of improvement from baseline achieved using an exact point estimate and 1-sided upper 95% confidence interval. The sample size for the primary objective was calculated based on the following assumptions:

The standard normal approximation to the 95% confidence interval associated with an estimate of a binomial parameter (p) is given by:

95% Confidence Interval: p ± 1.96 [ p (1 − p) / n ]^1/2^

To meet the enrollment goals for the BIO-AffectDX study, target enrollment percentages within each AF subtype and based on prior use of CRT-DX systems are defined as 50%, 30%, and 20% of the total study population for paroxysmal, persistent, and long-standing persistent AF, respectively. Therefore, it is expected that no single AF subtype will be greater than 60% of the total study population.

A limitation of using the above method is that secondary and subanalyses are exploratory and will not be adequately powered. This will be mentioned in all results, with confidence intervals and effect sizes also given to provide complete transparency, with a clear distinction that owing to small samples, the results likely overestimate the true effect size in the population.

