**Figure 2 fig2:**
[figure not shown]
Hierarchy of clinical composite score. NYHA = New York Heart Association classification; PGA = Patient Global Assessment.

In the BIO-AffectDX study, subjects will be analyzed on both an intention-to-treat and an as-treated basis to account for removal or exchange of the implanted CRT-DX device system. The primary analysis for the primary objective will include the entire cohort, including all AF subtypes. Secondary objective analysis for each AF subtype (ie, paroxysmal AF, persistent AF, and long-standing persistent AF) subgroup will utilize the subtype documented at the baseline medical history collection using the intention-to-treat population.

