Several prespecified and preplanned exploratory subgroup analyses on primary and secondary objective data will also be performed, when it is determined feasible and appropriate based on the available data The prespecified subgroups may include, but are not limited to, the following: AF subtype, AF burden, age, sex, race, NYHA class, LV ejection fraction, type of cardiomyopathy, QRS type and duration, ablation type and status, LV lead position and pacing vector, DX lead tip position in addition to the atrial dipole position (based upon operator visual assessment as high atrium, mid atrium, low atrium, or other), number of hospitalizations within the last 12 months, number of HF or arrhythmia hospitalizations within the last 12 months, ventricular pacing percentage, left atrial size and LV dimensions obtained during baseline echocardiography, degree of mitral regurgitation, and clinically relevant echocardiographic data. Additionally, study objective outcomes may be compared to rates from published literature and/or outcomes from a contemporary control group of subjects in sinus rhythm receiving a CRT-D. Daily remote monitoring data, including but not limited to AF burden and ventricular arrhythmias, will be obtained throughout the study participation. A variety of analyses will be conducted on the subgroups depending on the structure of the data and given normality. For categorical data this includes χ^2^, binomial proportion test, and McNemar test, while for continuous data includes paired *t* test, *t* test, and 2-sample *t* test. If the assumption of normality is not met, then nonparametric versions of the appropriate method will be used. Effect sizes and 95% confidence intervals will be given for all results of the subanalyses. An alpha of 0.05 will be used, and all analysis will be conducted with SAS 9.4 (SAS Institute Inc, Cary, NC).

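### The emphasised three-way AF-subtype comparison is paired with continuous-data tests for at most two samples, and the caveat promised for all results wrongly says that small samples likely overestimate effects

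*Protocol article*

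**What the plan says.** All references are to the protocol article.

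- **Emphasis.** The Introduction (Two-lead CRT system) says: "The analysis particularly emphasizes a comparison of patient outcomes between the AF subtypes". The second secondary objective (Objectives) is "to compare AF subtypes for CCS status, changes in Atrial Fibrillation Effect on Quality-of-Life Questionnaire, changes in Minnesota Living with Heart Failure Questionnaire", and continues with NYHA class, 6-minute walk and AF burden. That makes six outcomes at 6 and 12 months, five of them as changes.
- **Groups.** General considerations: "Target enrollment percentages are 50%, 30%, and 20% of the total study population for paroxysmal, persistent, and long-standing persistent AF, respectively". Sample size justification: "It is anticipated that at least 400 subjects will be implanted and followed through 12 months postimplantation at up to 50 US sites". Data analysis says that the subtype analysis "will utilize the subtype documented at the baseline medical history collection using the intention-to-treat population".
- **Tests.** Data analysis lists AF subtype first among the possible subgroups. It then names, for categorical data, chi-square, "binomial proportion test, and McNemar test, while for continuous data includes paired" t, plain t and two-sample t tests, with nonparametric counterparts if normality fails. Alpha is 0.05.
- **Caveat.** Sample size justification says that secondary and subgroup results will carry a warning that "owing to small samples, the results likely overestimate the true effect size in the population".
- **Other safeguards.** The study is called hypothesis generating (General considerations). Secondary and subgroup analyses are called exploratory and not adequately powered (Sample size justification). Effect sizes and 95% confidence intervals are promised (Sample size justification and Data analysis).

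**The concern.** There are two separate problems.

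First, the comparison that the article puts forward has three groups, but none of the tests it names for continuous data compares more than two. Applied to quality of life (AFEQT, MLHFQ), 6-minute walk and AF burden, the list leaves only pairwise testing, each pair at 0.05. This raises the chance of declaring a subtype difference where none exists. The article expects its results to inform consensus and guidance documents.

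Second, the promised caveat gives the wrong reason and a single direction. A reader told that every estimate is probably too large will discount all of them, including those that confounding has biased towards zero. The reader is not told about the mechanism that does exaggerate effects, which is attention to whichever comparisons reach significance.

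**Working it through.** **Inputs.** Group sizes from the target percentages: 0.50 × 400 = 200, 0.30 × 400 = 120, 0.20 × 400 = 80. Alpha is 0.05, taken as two-sided because the article does not state sidedness. The article gives no SD, effect size or correlation for this comparison, so those below are assumptions in SD units. It states no figure of its own for the subtype comparison that could be reproduced.

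**1. Error from pairwise testing.** Three pooled t tests at n = 200, 120 and 80, simulated 40,000 times with no true difference:

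- each test alone rejects in about 5% (5.1%, 5.0%, 4.9%);
- at least one of the three rejects in 12.0%. If the tests were independent this would be 1 − 0.95³ = 14.3%; shared groups make them correlated.
- One three-group test at 0.05 gives 5%.

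**2. Across the objective.** Chi-square already handles three groups for CCS status and NYHA category: 2 outcomes × 2 visits = 4 tests. The four continuous outcomes tested pairwise give 4 × 2 × 3 = 24. In total 28 tests:

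- expected false positives 28 × 0.05 = 1.4;
- chance of at least one, if independent, 1 − 0.95²⁸ = 76%.

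With one three-group test per outcome and visit there are 12 tests, and 1 − 0.95¹² = 46%. Both percentages are upper guides, because the outcomes are correlated (CCS contains NYHA class, and each outcome is measured twice in the same people).

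**3. What small groups do.** The half-width of a 95% interval for a proportion of 0.5, by the article's own formula 1.96·√[p(1 − p)/n], is 6.9 points at n = 200, 8.9 at n = 120 and 11.0 at n = 80. It extends equally in both directions.

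The difference detectable with 80% power is (1.96 + 0.84)·√(1/n₁ + 1/n₂): 0.32 SD (200 v 120), 0.37 SD (200 v 80) and 0.40 SD (120 v 80).

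**4. Is the effect overestimated?** Simulated mean of the estimated difference, over all results and over those with p < 0.05 only, across the three pairs:

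| True difference | Mean, all results | Ratio to truth, significant results only |
|---|---|---|
| 0.2 SD | 0.20 | 1.55 to 1.86 |
| 0.3 SD | 0.30 | 1.17 to 1.35 |
| 0.5 SD | 0.50 | 1.01 to 1.04 |

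Taken over all results, the estimate is unbiased. Even the standardised difference has a small-sample bias below 0.4%. Exaggeration appears only after selection on significance, and it is large only when the true effect is small.

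**5. Why the use of the baseline value should be fixed.** With equal SDs at baseline and follow-up, a baseline imbalance D and a correlation r, change-score and baseline-adjusted contrasts differ by D(1 − r). For assumed D of 0.2 to 0.5 SD and r of 0.3 to 0.7 the gap runs from 0.2 × 0.3 = 0.06 to 0.5 × 0.7 = 0.35 SD. The upper end is of the same order as the detectable differences in step 3. In non-randomised groups the two contrasts answer different questions, so the choice should be made in advance.

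**The case against.** The strongest reply is that this is a condensed article about an exploratory, observational study. It calls its results hypothesis generating, calls the secondary and subgroup analyses underpowered, and promises intervals and effect sizes. The test list belongs to the subgroup analyses and is introduced as covering a variety of analyses, while descriptive statistics are planned for all objectives. Models, covariates and missing-data rules can sit in the full protocol or SAP.

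Much of this stands, and it rules out several stronger readings:

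- *That the faulty caveat is the only safeguard.* It is not; the labels and intervals just mentioned are also there.
- *That the comparison will be unadjusted, or restricted to subjects with complete visits.* The article names no adjusted method, but it excludes none and states no complete-case rule. Its silence is not evidence.
- *That all six outcomes will be tested pairwise, giving 36 tests and an 84% chance of a false positive under independence.* Chi-square covers three groups for CCS and NYHA, so the count is 28 and the figure 76%.
- *That the t tests are definitely the method for the secondary objective.* This is likely, since AF subtype is a listed subgroup and the subgroup analyses extend to secondary-objective data, but it is not stated.

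The reply does not remove the two core points. Where the article does name continuous-data methods, they do not fit its own three-group question. The overestimation sentence is wrong as written, whatever an unseen SAP contains. An exploratory label corrects neither.

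**Conclusion.** The point holds in two parts.

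The caveat is wrong on the text alone. At the planned group sizes, estimates are imprecise but not inflated. Inflation of about 1.5 to 1.9 times arises only among results selected for significance when the true difference is near 0.2 SD, and it almost vanishes at 0.5 SD. Confounding may act in either direction.

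The test list does not match the emphasised comparison for the continuous outcomes. If it is applied there, family-wise error is about 12% per outcome and visit instead of 5%. This rests on the target enrolment split, two-sided testing, normal data with equal variances, and the likely but unstated use of those tests for the subtype comparison.

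The matter concerns secondary, exploratory results and leaves the primary estimate untouched. It should be corrected because it changes what is reported on the question that the article stresses.

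**What to change.** 1. For AFEQT, MLHFQ, 6-minute walk and AF burden, specify one three-group model per outcome with the baseline value as covariate (ANCOVA, or a repeated-measures model across visits). Use a single 2-df subtype test at 12 months, and read pairwise contrasts only if it is below 0.05. With three groups this holds the family-wise error for that outcome at 5%. Give the 6-month contrasts as estimates with intervals. For AF burden, define the baseline first, because pre-implant patch and Holter results are collected only if available.
2. Keep chi-square for CCS status and NYHA category.
3. As a sensitivity analysis, show the unadjusted estimates beside an analysis adjusted for baseline covariates that every subject has, such as age, sex and baseline NYHA class. LVEF is not guaranteed, since echocardiograms are also collected only if available.
4. Replace the caveat with: *estimates are imprecise and may be confounded; those singled out for significance tend to be exaggerated.*

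The cost is analysis wording, standard SAS procedures and slightly more analysis work, with no additional patients or data. One limit remains: six 12-month three-group tests still carry up to 1 − 0.95⁶ = 26% across outcomes under independence. The report should say so and keep the exploratory label.
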